## Study design and setting

2

A cRCT was conducted with randomization within schools at the classroom level to minimize confounding from school-level factors. The study comprised two phases: an initial phase (2023–2024) including 10 schools (66 classrooms), and a main study period (2024–2025) including 26 schools (162 classrooms). As shown in Figure 1, classrooms within a school were manually clustered to optimize comparability, with each school contributing one or more clusters and each cluster restricted to classrooms within the same building and sharing identical ventilation systems and flooring types. Flooring types were matched specifically to avoid differences in particle resuspension and aerosol dispersion. Following these primary clustering criteria, additional classroom characteristics, including floor level, orientation, classroom size, student number and age group, were considered.

**Figure 1 fig1:**
[figure not shown]
Study design and timeline of the intervention cluster-randomized controlled trial. Classrooms with similar characteristics were grouped into clusters and randomly assigned one of three study conditions: HEPA filter, ionization/plasma, or control. The 14-week study included a 3-week baseline (PACs off), three 3-week intervention phases (PACs on), and a 2-week post-intervention period (PACs off).

Each cluster was then randomly assigned to one of three study conditions: (1) HEPA filter PACs, (2) ionization/plasma PACs, or (3) control, i.e., no PACs (Figure 1). A dual-control design was used, with a control sample collected in each classroom during either the three-week baseline period prior to the intervention or the two-week post-intervention period, alongside a continuously monitored control group throughout the full 14-week study (Figure 1). In the initial study phase, the number and duration of intervention periods varied by school (ranging from one to four interventions), whereas in the main study period, each classroom underwent a three-week baseline followed by three repeated three-week intervention periods.

### School recruitment and selection

2.1

For the main study period (2024–2025), out of an estimated 6,500 primary schools in the Netherlands (56), approximately 1,700 primary schools within feasible operational reach of Utrecht were contacted. Schools for special education and Kindergarten classes (children aged ~4–6 years) were excluded. Of the contacted schools, 213 replied; 185 declined participation, and 28 expressed interest. Schools were included if they had at least three comparable classrooms to be randomized in the study. Two schools were later excluded due to process-based reasons: one school refused to provide essential study information, and one withdrew before final agreement. The final study population of the main study period comprised of 26 schools. The inclusion/exclusion process is depicted in Figure 2.

**Figure 2 fig2:**
[figure not shown]
Flowchart showing the recruitment and selection of schools for inclusion in the cRCT. Schools were included if they had at least three comparable classrooms; Kindergarten classes were excluded due to differences in occupancy patterns and activity types affecting bioaerosol dynamics (57).

Participating schools were spread across multiple provinces in the Netherlands (Figure 3) and varied in classroom sizes, ventilation systems, student numbers, and special features such as flexible grouping and air conditioning units (Table 2). Ventilation type was classified as natural, mechanical (balanced with supply and exhaust), mechanical (exhaust only), or unknown, based on interviews with school contacts and on-site observations. An initial study phase (Dec 2023-May 2024) was conducted in 11 schools and 69 classrooms; one school from this phase is to be excluded from subsequent analyses due to a prolonged delay between baseline and intervention measurements, rendering them temporally non-comparable with the other schools due to seasonal differences in viral circulation and classroom ventilation behavior. This results in 10 schools and 66 classrooms in the initial phase. The main study period (Oct 2024–May 2025) comprised 26 schools and 162 classrooms. Across both study phases, 180 classrooms participated, with 48 of the classrooms participating in both years.

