## Abstract

In school environments, characterized by high occupancy and prolonged exposure, airborne contaminants pose risks to respiratory health and learning outcomes. Portable air cleaners (PACs) are increasingly considered as a supplement to ventilation, yet field-based evidence remains heterogeneous, with few randomized trials and limited data on microbial agents. Here, we describe the design and methodology of a large-scale cluster-randomized controlled trial evaluating PAC effectiveness in Dutch primary school classrooms. The study included 180 classrooms across 29 primary schools, with classrooms clustered within schools and randomized to HEPA-filter PACs, ionization/plasma PACs, or no PACs. The design incorporated a three-week baseline or two-week post-intervention control period, and three repeated three-week intervention periods in the main phase, totaling up to 14 weeks per school. PACs were pre-tested under standardized laboratory conditions, screened for safety, and operated at comparable clean air delivery rates (CADR). Airborne dust was collected using electrostatic dust fall collectors (EDCs) and analyzed for bacterial markers representing common human microbiome constituents, a general bacterial indicator, and viral markers for seasonal infections. In 12 classrooms, active air sampling was conducted alongside EDCs to validate and quantify passive measurements. Continuous monitoring of particulate matter (PM₁₀, PM₄, PM₂.₅, PM₁), CO₂, air temperature, relative humidity, and volatile organic compounds (VOCs) was performed. Classroom-level absenteeism and parent-reported respiratory symptoms were collected retrospectively. Weekly national infectious-disease surveillance and outdoor PM and NO₂ data will contextualize indoor measurements and health outcomes. Hierarchical mixed-effects models accounting for school, cluster, and classroom structure will analyze microbial outcomes. Bayesian hierarchical models may be applied for values outside the quantifiable range. By integrating comprehensive indoor air quality assessment with a dual-control design distinguishing pre-existing classroom differences from temporal trends, this registered trial (ClinicalTrials.gov, NCT07479420; 6 March 2026) provides a rigorous framework to evaluate PACs under real-world classroom conditions and support evidence-informed strategies to improve classroom indoor air quality.

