### Air cleaner deployment and monitoring

3.2

PACs were intended to be positioned according to the partner companies’ recommendations for optimal cleaning efficiency which varied between devices due to differences in airflow configuration and design. However in practice placement was largely dictated by practical constraints such as available space classroom layout and to a minor extent by availability of power outlets. Consequently PAC placement was not fully standardized across classrooms but rather reflected realistic implementation conditions in occupied school environments. Teachers were instructed to keep the devices operational at all times and asked to document any temporary shutdowns or adjustments to lower settings on a standardized log form. Beyond this schools could continue their usual routines and no modifications to ventilation practices were instructed. In addition during each three-week routine sample collection (described below) the operational status and settings of the devices were systematically recorded by the research team. For schools using the PACs over extended periods devices requiring maintenance were attended to after the summer holiday following the manufacturer’s standard procedures to ensure consistent performance. Additionally TU/e conducted follow-up performance testing of all devices at the end of the study period to verify sustained air cleaning efficacy. Blinding of students and school staff was not feasible as air cleaners without active filtration could not be provided across all participating partner companies.

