## Data analysis plan

6

All analyses will be performed in RStudio [version 4.5.1 (83)]. The project will use the UU network drive for secure data archiving, with access restricted to authorized study personnel. Data were coded using consistent study identifiers prior to analysis, with a separate pseudonymization key linking identifiers to study sites.

Intervention effects taking into account data of all participating schools will be assessed using generalized linear mixed-effects models (GLMMs) with random intercepts for school, cluster, and classroom, reflecting the hierarchical clustering inherent to the study design. Residual normality and homoscedasticity will be verified, applying log transformation when necessary to meet model assumptions. To account for temporal correlation between successive intervention periods within classrooms, autoregressive structures [e.g., AR (1)] will be considered, with their inclusion guided by both model fit and the anticipated influence of seasonal variation. Potential covariates, including grade, classroom dimensions, number of students, student density, lesson hours, floor level, urbanization, ventilation type, and flooring type will be evaluated in univariate GLMMs containing intervention arms and random effects. Covariates significantly impacting intervention estimates or model fit may be considered for inclusion in the final multivariable model, guided by both statistical evidence and conceptual relevance. ACH will be considered as a potential covariate in the mixed-effects models to account for differences in baseline ventilation and may be evaluated as a continuous variable or categorized into predefined ranges (ACH-bins). Multicollinearity will be assessed, with highly correlated variables excluded to ensure model stability, and the final model will be selected based on overall fit (AIC, likelihood ratio tests).

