Sensitivity analyses will assess model robustness by re-fitting the final models after exclusion of outliers (identified by influence diagnostics), exclusion of baseline measurements, and restriction to the 2024–2025 sampling period only. An additional sensitivity analysis will be performed to assess the robustness of the findings under protocol-compliant PAC operation. Only measurements without indication of incorrect PAC operation are included, based on the recorded device settings during sample placement and collection by the research team and the absence of reported deviations in the teacher log forms.

Data analysis of species-specific bacterial and viral markers will be guided by observed detection levels. Where quantitative measurements permit, marker concentrations will be analyzed using GLMMs as described above. If detection within the quantifiable range is limited, outcomes will be modeled as binary (detected or non-detected) using logistic mixed-effects models with random effects for school, cluster, and classroom, and fixed effects for the intervention arms. Appropriate model assumptions and hierarchical variance structures will be considered. Correlations between markers may be examined to explore co-detection patterns. Missing data will not be imputed; analyses will use available data within mixed-effects models.

In addition to standard GLMM or binary logistic mixed-effects models, Bayesian hierarchical models may be applied to species-specific outcomes as continuous variables, allowing incorporation of observations outside the quantifiable range while still leveraging the information from measurable values. Observations within the quantifiable range will be treated as measured values, whereas non-detects or values outside of the quantifiable range, will be incorporated as censored data, reflecting the uncertainty in the true underlying value. Feasibility of using a Bayesian approach in this case depends on sufficient informative observations within the measurable range. Random intercepts for school, cluster and classroom will account for the hierarchical structure. Priors for intercepts, intervention effects, residual variance, and group-level variance will be informed by plausible ranges derived from the quantifiable data. Model fit will be evaluated via posterior predictive checks, and sensitivity analyses may explore the impact of prior choices and censoring assumptions.

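### Forty-eight of the 180 classrooms were followed in two school years, but the stated main model has one classroom intercept and names no year or classroom-by-year term

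*Protocol article*

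**What the plan says.** **Counts.** Section 2.1 gives, for the first season, "This results in 10 schools and 66 classrooms in the initial phase" and, for the second, "The main study period (Oct 2024–May 2025) comprised 26 schools and 162 classrooms". It then states: "Across both study phases, 180 classrooms participated, with 48 of the classrooms participating in both years". The Abstract states "The study included 180 classrooms across 29 primary schools". Returning rooms are counted once, and sections 3.1, 4.1 and 4.4 also use 180 as their denominator.

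**Main model.** Section 6 pools all participating schools in mixed models "with random intercepts for school, cluster, and classroom, reflecting the hierarchical clustering inherent to the study design". An AR(1) structure is optional and is described for successive intervention periods. The candidate covariates include grade and number of students, but not school year, phase or earlier air-cleaner use.

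**Baseline and earlier use.** Section 2 gives every main-phase classroom a three-week baseline, which Figure 1 defines as air cleaners off. Section 3.2 adds: "For schools using the PACs over extended periods devices requiring maintenance were attended to after the summer holiday". Section 4.5 notes that the 2023-2024 winter was an intervention period in some schools, but only in connection with the parent survey.

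**Sensitivity analyses.** Section 6 plans a refit under "restriction to the 2024–2025 sampling period only" and a refit that leaves out the baseline measurements.

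**Not stated.** The article does not say whether returning rooms kept their arm or were randomised again, how long the devices had been off before a second-year baseline, or whether the classroom effect is indexed by room or by room and year.

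**The concern.** The bacterial targets are constituents of the human microbiome (section 4.2), so what settles in a room depends on who occupies it. A classroom normally holds a different class each school year. The laboratory also changed its qPCR platform between phases. Samples from the same room and the same year are therefore likely to be more alike than samples from the same room in different years. A single room intercept cannot represent this. If a room was in one arm in one year and another arm in the next, the model treats the year-to-year difference within the room as a precise within-room contrast between arms.

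The second issue is the role of the baseline. Section 7 relies on the non-intervention sample to show pre-existing differences between classrooms. In a returning air-cleaner room that sample may come after a season of treatment. Any persisting effect would lower that room's baseline and shrink the before/after part of the contrast.

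At stake are the error rate of the main test and, to a smaller degree, the size of the estimated effect.

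**Working it through.** **1. The article's counts, reproduced**
- Unique classrooms: 66 + 162 − 48 = 180, as stated.
- Classroom-years: 66 + 162 = 228. From returning rooms: 2 × 48 = 96, and 96/228 = 42.1%.
- Returning rooms as a share of the main phase: 48/162 = 29.6%.
- Schools in both phases: 10 + 26 − 29 = 7.
- First-entry classroom-years: 66 + (162 − 48) = 66 + 114 = 180.

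**2. Effect of a room-only intercept on the test**

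The article gives no variance components, so all variances here are assumptions on the log scale.

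*Analytic calculation.* Layout: 60 clusters of three rooms (16 in both years, 6 initial only, 38 main only), with four samples per classroom-year, or three without the baseline. Variances: cluster 0.10, room 0 to 0.05, class-year 0.05 to 0.20, residual 0.30. The room-only model's limiting variances were found, and its model-based SE was compared with the sandwich SE. With r = model SE / true SE, the actual size of the test is 2Φ(−1.96 r).
- Arms changed between years: r = 0.77 to 0.94. At r = 0.77, 2Φ(−1.51) ≈ 13%. At r = 0.94, 2Φ(−1.84) ≈ 6.6% (ratios rounded).
- Arms kept: r = 1.00 to 1.05. At r = 1.05, 2Φ(−2.06) ≈ 4.0%, so the size is 4.0% to 5.0%.
- With room variance fixed at 0.05, the sizes are about 6-12% and 4.0-4.9%.

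*Simulation.* 180 rooms, 228 room-years, four samples each, room variance 0.10, residual 0.30, fixed period and year effects, air-cleaner arms pooled 2:1 against control, no school or cluster level. There were 1,500 runs, so the Monte Carlo SE near 5% is √(0.05 × 0.95/1500) = 0.56 percentage points. Null rejection at nominal 5%:

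| Room-by-year variance | Arms re-drawn: room intercept | Arms re-drawn: room-year intercept | Arms kept: room intercept | Arms kept: room-year intercept |
|---|---|---|---|---|
| 0 | 4.8% | 4.4% | 6.2% | 7.9% |
| 0.10 | 8.3% | 5.4% | 4.5% | 6.2% |
| 0.20 | 12.3% | 5.1% | 5.2% | 7.0% |

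The simulated model already contained a fixed year effect, so the inflation comes from the missing room-by-year term alone. The last column shows that swapping room for room-year is not the answer when arms were kept. Both levels are needed.

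**3. Carry-over into the second-year baseline**

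Assume equal three-arm allocation and arms kept.
- Returning rooms with earlier air-cleaner use: 48 × 2/3 = 32, which is 32/162 = 19.8% of main-phase rooms.
- Main-phase air-cleaner rooms: 162 × 2/3 = 108, and 32/108 = 29.6%.

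Take a true reduction of 20% (the effect size in section 5) and let a fraction c of it persist at the second baseline.
- Pure before/after contrast, main phase: 1 − exp[ln(0.8)(1 − 0.296c)]. For c = 0.5 this is 17.3%. For c = 1 it is 14.5%.
- Pooled room-intercept model, 500 runs: mean log effect −0.2168 at c = 0.5, so 1 − exp(−0.2168) = 19.5%. At c = 1 it is −0.2061, so 18.6%.
- 2024-2025 data only, c = 1: −0.2029, so 18.4%. The restriction does not remove carry-over.

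**4. What the planned refits cover**

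| Refit | Shared intercept across years | Second-year baseline after earlier use |
|---|---|---|
| 2024-2025 only | removed | remains |
| Without baselines | remains | removed |

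**The case against.** Several points on the other side are sound.

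- **Index of the classroom effect.** The article does not define it, and a condensed article may leave this to a fuller plan. Section 6 also says that variance structures will be considered. But the structure it names stops at classroom, and returning rooms are counted once throughout. A reader who follows the text would fit one intercept per room.
- **The two harms need opposite conditions.** Error inflation needs arms that changed between years. A baseline shift confined to air-cleaner rooms needs arms that were kept. They should not be added together.
- **Planned safeguards exist.** Each problem is removed by one of the two refits. Grade and number of students, and an AR(1) term if used, could absorb part of the class-year variation. These are optional terms or sensitivity analyses, so the main model stays as written.
- **Carry-over is uncertain.** Section 3.2 does not say how many schools used the devices for extended periods, that these were the 48 rooms, or that devices ran until the second baseline. About a third of the 48 were probably controls in the first year.

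Two stronger readings are tempting. A reader might infer that the plan treats returning rooms as never having had an air cleaner. The article makes no such claim: it defines baseline only as devices off, and section 4.5 acknowledges earlier intervention. A reader might also infer that the standard errors are wrong in every case. With arms kept, the analytic calculation shows them correct or slightly too large.

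**Conclusion.** The point holds in a limited form. The stated main model has no level for classroom-by-school-year, although 42% of classroom-years come from rooms followed twice. Under the assumed variances, the arm-effect test runs at about 6-13% instead of 5% if returning rooms changed arm, and at about 4-5% if they kept it. The article does not allow a choice between these cases. If arms were kept, carry-over may bias the estimate modestly towards no effect: a true 20% reduction is estimated as about 18.6% in the pooled model even if the whole effect persists.

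The counts are exact. The error rates and carry-over sizes rest on assumed variances, equal allocation and assumed persistence, and new occupants each year are inferred. This should be corrected before the analysis, but it does not invalidate the design.

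**What to change.** - **Section 6, main model:** use random intercepts for school, cluster, classroom, and classroom-by-school-year nested in classroom, with a fixed phase effect. The phase effect takes up any shift common to all rooms, such as the change of qPCR machine. The nested term takes up what is specific to a room in a given year.
- **Section 2 or 6:** state whether returning rooms kept their arm or were randomised again.
- **Section 6, sensitivity analyses:** add a refit without the second-season data of the 48 returning rooms, leaving 114 + 66 = 180 first-entry classroom-years. This removes the shared intercept and the doubtful second baselines together.
- **Reporting:** give air-cleaner status before each second-year baseline.

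The cost is one random term, one fixed term and one extra model run on data already collected, with somewhat wider intervals in the first-entry analysis.

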**Figure 3 fig3:**
[figure not shown]
Geographic distribution of participating and excluded schools across study periods. Orange pins indicate the initial-phase sites (2023-2024), blue the main-phase sites (2024-2025), green those participating in both phases, and a gray pin denoting a school excluded due to non-comparable measurement timing.

**Table 2 tab2:** Study characteristics of participating schools.

Characteristics	Initial study phase (2023–2024)	Main study phase (2024–2025)
Schools (n)	10	26
Geographic setting ^1^		
Extremely urbanized	10.0%	26.9%
Strongly urbanized	30.0%	23.1%
Moderately urbanized	20.0%	30.8%
Hardly urbanized	40.0%	19.2%
Classrooms (n)	66	162
Classroom surface area (m^2^) ^2^	50.3 [47.0–56.0], 38.9–60.6	51.4 [42.4–56.1], 35.1–76.4
Classroom volume (m^3^) ^2^	157.5 [149.4–186.6], 115.0–236.7	156.2 [129.2–182.0], 95.1–242.9
Ventilation system		
Natural	22.7%	11.1%
Mechanical (balanced)	22.7%	3.7%
Mechanical (type unknown)	27.3%	74.1%
Mechanical (exhaust only)	27.3%	11.1%
Special features		
Carpet flooring	2 clusters	2 clusters
Open-plan learning spaces	N. A.	1 school
Combination class in afternoons	N. A.	1 school
Air conditioning units	2 classrooms	2 classrooms
Students per classroom ^2^^,^ ^3^	27 [23–28], 17–32	24 [22–27], 9–37
Grade ^2^	6 [5–7], 3–8	6 [4–7], 3–8

1 Urbanization level classified according to address density (addresses per km^2^) as defined by Statistics Netherlands (CBS): extremely urbanized (≥ 2,500), strongly urbanized (1,500–2,500), moderately urbanized (1,000–1,500), hardly urbanized (500–1,000), and non-urbanized (rural) (< 500) (105).

2 The following is reported: median [IQR], min–max.

3 Student numbers per classroom were determined via desk counts and could fluctuate across measurement periods; values were averaged per class, with min and max reflecting the lowest and highest observed counts in any period.

